**Results:**

The primary goal of this study is to assess the feasibility of the treatments in patients with Parkinson's disease by measuring serious RIC-related adverse events and any reduced incidence of adverse events during the trial and to study potential efficacy, improvement of patients' excessive daytime sleepiness, quality of life-based on ESS, PSQI, PDSS-2, and PDQ39 scores. The secondary goal is to confirm the safety of the treatments.

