### Outcomes

#### Outcomes for feasibility and efficacy

The primary outcomes of this study are to assess the feasibility and efficacy of RIC from changes of ESS, PSQI, PDSS-2, and PDQ39 scores from the baselines to post-treatment on days 7, 14, 28, or 90. This study will determine (1) whether ESS, PSQI, PDSS-2, and PDQ39 can be performed in the patients and (2) the differences between ESS, PSQI, PDSS-2, and PDQ39 in patients with or without RIC. Certified therapists and assistants will collect data from the subjects and the obtained information will be used for statistical analysis.

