#### Outcomes for safety

The secondary outcome of this study is to assess the safety of RIC. Any serious RIC-related adverse events are the following: (1) inability to tolerate RIC or sham-RIC procedures leading to the suspension of the study; (2) signs of tissue or neurovascular injury caused by RIC and sham RIC operations (e.g., palpation of distal radial artery pulsation, visual inspection of local edema, erythema and skin damage, or palpation of tenderness). All adverse events will be independently determined by trained individuals of the research group who are blinded by random grouping.

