### Sample size estimation

This is a phase 1 test measuring the safety and feasibility of RIC. Because there has not been a clinical study on RIC for Parkinson's patients, there is no data for reference at this point. Hertzog (48) suggests that 10–20 patients in each group are enough to evaluate the feasibility of a pilot study. Dobkin et al. explain that most phase 1 clinical rehabilitation pilot studies start with samples of 6–12 participants (49). Based on studies addressing the safety and feasibility of RIC, this project targets 20 patients in each group. The results of this study will be used not only to determine the safety and feasibility of RIC but also to estimate the sample size and calculate the power required for the phase 2 test in the future.

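### Feasibility of RIC, a primary objective, is defined inconsistently and could be concluded from efficacy scores, while its nearest direct measure sits under secondary safety

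*Protocol article*

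**What the plan says.** The protocol article describes feasibility in three places and safety in two.

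- **Outcomes for feasibility and efficacy.** One primary outcome covers both concepts: "The primary outcomes of this study are to assess the feasibility and efficacy of RIC from changes of ESS, PSQI, PDSS-2, and PDQ39 scores", at days 7, 14, 28 or 90. Two questions follow. The first is "whether ESS, PSQI, PDSS-2, and PDQ39 can be performed in the patients"; the second is the difference in the scales with and without RIC.
- **Abstract, Results.** The primary goal is given in these words: "assess the feasibility of the treatments in patients with Parkinson's disease by measuring serious RIC-related adverse events". A lower frequency of adverse events is named as a further measure. The four scales appear there under potential efficacy. The paragraph ends: "The secondary goal is to confirm the safety of the treatments".
- **Outcomes for safety.** "The secondary outcome of this study is to assess the safety of RIC". Serious RIC-related adverse events are listed here. The first item is inability to tolerate the RIC or sham procedure, leading to suspension; the second is signs of tissue or neurovascular injury.
- **Sample size estimation.** "This is a phase 1 test measuring the safety and feasibility of RIC". The 20 patients per group rest on pilot-study rules of thumb, and the results are meant to inform the size and power of a phase 2 trial.
- **Statistical analysis.** Data come from patients who complete the protocol and follow-up, and the analysis is per protocol.

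**The concern.** A study justified as a test of feasibility needs one statement of what feasibility means. This article gives two, and each is borrowed from another concept. The Outcomes section reads feasibility from score changes, which are the efficacy measure. The Abstract reads it from adverse events, which are the safety measure. The only other element, whether the scales can be performed, describes the questionnaires and not the cuff procedure.

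A treatment can be fully deliverable and leave ESS unchanged. Equally, ESS can improve among the patients who persisted while many others gave up. As written, a between-group difference in scores could be reported as evidence that RIC is feasible, or the definition could be chosen after the data are seen. The completers rule adds to this, because the patients most informative about feasibility are those who stop.

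**Working it through.** The point is one of definition, so the main check sets the sections side by side. The article gives no effect size, SD, power, dropout rate or feasibility criterion, so there is no sample-size calculation to reproduce. The stated totals agree: 2 × 20 = 40, and 20 lies within the 10 to 20 per group that the article cites.

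**Step 1. What each stated measure tells us about RIC feasibility**

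| Stated measure | Section and rank | What it measures |
|---|---|---|
| Change in ESS, PSQI, PDSS-2, PDQ39 | Outcomes for feasibility and efficacy: primary, as feasibility and efficacy. Abstract: potential efficacy | Efficacy |
| Whether the four scales can be performed | Outcomes for feasibility and efficacy: primary | Feasibility of the assessments |
| Serious RIC-related adverse events | Abstract: primary, as feasibility. Outcomes for safety: secondary | Safety |
| Intolerance leading to suspension (one of those events) | Outcomes for safety: secondary | Tolerability, the nearest measure of RIC feasibility |

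The first and third rows show the conflict. The Abstract and the Outcomes section attach different measures to feasibility, and the same events serve as a primary feasibility measure in one and a secondary safety measure in the other. The fourth row shows that a relevant measure exists but is not placed under feasibility in the Outcomes section.

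**Step 2. What has to be delivered**

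RIC is given once a day for 28 days (Study design) to 20 patients, so 20 × 28 = 560 RIC sessions are planned, with another 560 sham sessions. None of the outcomes stated in the article counts sessions delivered. Intolerance leading to suspension captures stopping for that reason, but not missed or partial sessions or withdrawal for other reasons.

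**Step 3. Effect of the completers rule**

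Assume, for illustration only, that k of 20 RIC patients stop for intolerance, that all others complete, and that suspension refers to the patient's own participation.

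- Completion in all randomised patients = (20 − k)/20.
- Completion in completers = (20 − k)/(20 − k) = 100% for any k below 20.
- Intolerance is k/20 in all randomised patients and 0/(20 − k) in completers.

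With k = 2, completion is 18/20 = 90% against 18/18, and intolerance is 2/20 = 10% against 0/18. With k = 4, completion is 16/20 = 80% against 16/16, and intolerance is 4/20 = 20% against 0/16.

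**Step 4. Precision of a delivery-based measure at the planned size**

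Exact (Clopper-Pearson) 95% limits for x of n are: lower = 0.025 quantile of Beta(x, n − x + 1); upper = 0.975 quantile of Beta(x + 1, n − x), with the upper limit set to 100% when x = n.

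| Completing RIC (assumed) | Proportion | Exact 95% CI |
|---|---|---|
| 20/20 | 100% | 83.2% to 100% |
| 18/20 | 90% | 68.3% to 98.8% |
| 16/20 | 80% | 56.3% to 94.3% |

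The intervals are wide, but a proportion in all randomised patients can be estimated and reported without enlarging the trial.

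**The case against.** The strongest case on the other side has four parts.

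- **Delivery is not ignored.** Intolerance leading to suspension is recorded, and the Abstract's Methods has it evaluated at days 7, 14, 28 and 90. This stands. A reader might infer that the feasibility question cannot be answered, or that the outcomes say nothing about delivery; the text does not support either. What remains is that this measure is filed under secondary safety and is exposed to the completers rule.
- **The Outcomes section can be read charitably.** Its first question could be taken as feasibility of the assessments and its second as efficacy. That is a fair reading of the two questions, but the opening sentence still says to "assess the feasibility and efficacy of RIC from changes of ESS, PSQI, PDSS-2, and PDQ39 scores". Reporting a score change as feasibility is therefore a possible consequence of the wording, not a certain one.
- **Safety is ranked consistently.** The Abstract and the Outcomes section both call it secondary. This stands: the conflict lies in using the same events as a primary feasibility measure, and it gives no ground for making safety co-primary.
- **An article condenses the full protocol.** Progression criteria, session records or a separate safety population may be set out elsewhere, so their absence here is not the point. Condensation does not explain two different stated definitions.

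A reader might also infer that the completers rule forces the answer on scale completability close to 100%. The article does not say which denominator that question uses, so this is not shown. Step 3 of the working concerns completion of treatment and intolerance only.

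**Conclusion.** The concern holds in this form: the article defines feasibility of RIC inconsistently, and the conclusion on a primary objective is ambiguous and could rest on efficacy scores. The nearest direct measure, intolerance leading to suspension, is ranked as secondary safety, and the only analysis population stated would leave out the patients who experience it.

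No stated figure is wrong and the planned 40 patients are unaffected. The size is best seen in the illustration: with 2 or 4 of 20 RIC patients stopping, completion of 90% or 80% in all randomised patients becomes 100% among completers. This assumes that suspension means the patient's own participation, that the completers rule applies to the feasibility and safety summaries as literally written, and that the stopping numbers are only examples. It is a matter to correct before analysis, because it concerns how a primary objective will be judged.

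**What to change.** - Use one definition of feasibility in the Abstract and in both Outcomes subsections, based on delivery of RIC. One example is the proportion of randomised patients in each arm who complete the planned sessions, with retention at days 28 and 90 and the number with intolerance leading to suspension.
- Count these in all randomised patients, not completers, and report exact 95% confidence intervals by arm.
- Keep changes in ESS, PSQI, PDSS-2 and PDQ39 as efficacy outcomes only. If completability of the scales is of interest, label it as feasibility of the assessments.
- Keep adverse events as safety outcomes at the rank already given. Intolerance leading to suspension can also be tabulated under feasibility if the text says so.
- If the full protocol already holds a criterion for judging RIC feasible, refer to it; if not, set one in advance.

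The cost is a change of wording and a tabulation of sessions delivered, which may need a simple session log if none exists. No extra patients or visits are needed.

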### Patient population

Participants will be recruited from outpatient and inpatient centers. The enrollment criteria are as follows: (1) diagnosis of Parkinson's disease according to MDS clinical criteria; (2) age of 18–90 year olds; (3) ESS score ≥10; (4) written informed consent obtained from the participants or legally authorized representative. Exclusion criteria are the following: (1) contraindication of ischemic conditioning (e.g., severe soft tissue injury, fracture, and peripheral vascular disease of bilateral upper extremities); (2) hemodynamic instability (i.e., systolic blood pressure > 180 mmHg, diastolic blood pressure > 110 mmHg, heart rate < 40 beats/min or > 100 beats/min, percutaneous oxygen saturation ≤ 92%, or body temperature ≥ 38.5°C); (3) life expectancy ≤ 1 year; (4) unstable comorbidities associated with the lungs, liver, and kidney (e.g., severe abnormal pulmonary function, hepatic insufficiency, renal insufficiency); (5) coagulopathy or active bleeding; (6) complications associated with acute coronary syndrome or severe arrhythmia; (7) pregnancy or nursing; (8) participation in another ongoing clinical trial.

Epworth Sleepiness Scale (ESS) is widely utilized in clinical settings to evaluate the severity of EDS. A score of 10 is typically used as a cutoff to indicate sleepiness with higher scores for more sleepiness (34). In this study, those with ESS ≥ 10 are recruited.

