### Statistical analysis

Data are obtained from all patients who complete the study protocols and follow-ups. They will be analyzed by per-protocol (PP) analysis. Statistical analysis will be performed using SPSS version 19 (SPSS Inc., Chicago, IL, USA). *P* < 0.05 will be considered statistically significant. Demographics and clinical characteristics will be analyzed for descriptive statistics. Continuous and categorical data will be presented as mean values, standard deviations, number values, and percentages. Continuous variables consistent with the normal distribution will be compared by the independent samples *t*-test or ANOVA or rank-sum test. Categorical variables will be compared by chi-square testing.

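### Efficacy is a primary outcome with no lead scale or visit: four scales at four visits under one P < 0.05 leave 16 candidate primary comparisons

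*Protocol article*

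**What the plan says.** Under *Outcomes for feasibility and efficacy*, the protocol article makes feasibility and efficacy the primary outcomes, to be judged "from changes of ESS, PSQI, PDSS-2, and PDQ39 scores from the baselines to post-treatment on days 7, 14, 28, or 90". It adds that the study will determine "the differences between ESS, PSQI, PDSS-2, and PDQ39 in patients with or without RIC". The Results paragraph of the abstract also places all four scores under the primary goal. Neither place singles out a scale or a visit.

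Under *Statistical analysis*, one threshold covers everything: P "< 0.05 will be considered statistically significant". Continuous variables "will be compared by the independent samples" t-test, by ANOVA or by a rank-sum test. No order of testing, adjustment or rule for success is given.

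Under *Sample size estimation*, the trial is described as a phase 1 test of safety and feasibility with 20 patients per group. Its results are also to be used for the sample size and power of a phase 2 trial.

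Under *Patient population*, ESS is the entry scale: "In this study, those with ESS ≥ 10 are recruited".

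**The concern.** A primary outcome should tell the reader which number will answer the question. This one leaves the number open. The visits are joined by *or*, so any of the four could be taken as the time point. The scales are joined by *and*, but nothing requires all four to show a difference. With one blanket threshold, a significant result on any scale at any visit could be presented as a finding on the primary outcome.

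Two things are at stake. The first is the error rate: the chance of some significant primary result with no true effect is well above 5%. The second is planning. Phase 2 can be sized only once a scale and a visit are chosen. If that choice is made after the data are seen and falls on the largest difference, the effect size carried forward will be too large.

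An unseen statistical analysis plan might specify an adjustment. The primary variable and its time point, however, are for the protocol to fix, and the article does state a definition. The problem is that the definition is open.

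**Working it through.** **Inputs from the protocol article.** Four scales and four visits (*Outcomes for feasibility and efficacy*). Threshold 0.05 (*Statistical analysis*). 20 per group (*Sample size estimation*), allocated 1:1 (*Randomization*).

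**Assumptions.** Two-sided tests, since sidedness is not stated. One two-sample t-test per scale per visit. Correlations between scales and between visits are not given, so a range is shown.

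**The plan's own figure.** The article states no family-wise error rate, effect size, standard deviation or power, so there is no error or power figure to reproduce. The 20 per group matches the top of the 10–20 per group that the article cites for pilot studies.

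**Step 1: count.** 4 scales × 4 visits = 16 comparisons.

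**Step 2: independent tests.**
- Any P < 0.05: 1 − 0.95^16 = 0.560, or 56%.
- Any P < 0.05 favouring RIC: 1 − 0.975^16 = 0.333, or 33%.
- For contrast, four scales at a single visit: 1 − 0.95^4 = 0.185, or 18.5%.

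**Step 3: correlated tests.** Scales and repeated visits in the same patients will be correlated, so 56% is an upper reference and not an expected value. The table comes from simulating 16 t-tests with no true effect, 20 per group and 20,000 runs per row. All visits share one correlation, all scales share another, and the two multiply.

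| Between visits | Between scales | Any P < 0.05 | Favouring RIC |
|---|---|---|---|
| 0.3 | 0.3 | 51% | 28% |
| 0.5 | 0.5 | 43% | 22% |
| 0.6 | 0.4 | 42% | 22% |
| 0.7 | 0.5 | 37% | 19% |
| 0.8 | 0.6 | 31% | 15% |
| 0.8 | 0.8 | 25% | 12% |
| 0.9 | 0.9 | 17% | 9% |

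The between-visit value can be partly anchored. The outcomes are changes from one shared baseline. If raw scores have equal variance σ² and equal correlation ρ across all visits, each change has variance 2σ²(1 − ρ) and any two changes have covariance σ²(1 − ρ). Their correlation is therefore 0.5 whatever ρ is. With 0.5 between visits, the chance of any P < 0.05 is 49% if the scales are uncorrelated and 43% if they correlate at 0.5.

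**Step 4: effect of picking the largest difference.** In the same kind of simulation with no true effect, the largest of the 16 standardised differences favouring RIC averages 0.52 (0.3/0.3), 0.45 (0.6 between visits, 0.4 between scales) and 0.30 (0.8/0.8). The true value in every case is 0.

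**Step 5: after a fix.**
- One named scale at one named visit: 5%.
- Bonferroni over 16: 0.05/16 = 0.0031 per test, family-wise error at most 5%.
- Power at 20 per group for a standardised difference of 0.9, chosen only for illustration (normal approximation): 81% with one primary test, 46% with Bonferroni over 16.

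**The case against.** The strongest reply is that this is a phase 1 pilot. The article claims no power and states no rule for success. Elsewhere it speaks only of potential efficacy, so holding it to confirmatory standards would be unfair. That lowers the consequence. It does not remove the point, because the outcomes section names efficacy as primary, a significance threshold is set, and the results feed phase 2.

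A second reply is that 16 separate tests is an inference. The article does not list 16 tests, does not say how visits will be handled, and offers three kinds of test. This stands, and the error rates above are conditional on one comparison per scale per visit.

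Three stronger readings are tempting and are not supported:

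- *A chance positive result is likely.* In these calculations the rate exceeds one half only with independent or weakly correlated tests. It also counts results favouring sham. For a result favouring RIC it is about 12–28% over the range 0.3 to 0.8.
- *The plan allows success on any scale or any visit.* *Or* joins only the visits, and no success rule is written. The text leaves the choice open but does not state that any one result will be called the primary one.
- *Phase 2 will be sized on the best of 16.* The article says only that the results will be used for sizing. Selecting the largest difference is a risk, not a stated plan.

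**Conclusion.** The concern holds as a defect in the primary outcome definition: efficacy is named as primary with no lead scale or visit, under one threshold of P < 0.05. If each scale is compared at each visit, the chance of at least one significant result with no true effect is 56% under independence. It is about 25–51% for assumed correlations of 0.3 to 0.8, against a nominal 5%. For a result favouring RIC it is about 12–28%, against 2.5%. Even at 0.9 for both correlations the overall rate is 17%, more than three times nominal. The exact figure cannot be known from the article; that it is well above 5% holds across the whole range examined.

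Because the trial is a pilot, the main practical harm is to interpretation and to phase 2 planning. It is not a false confirmatory claim.

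A minor wording point goes with this: days 7 and 14 are labelled post-treatment although treatment runs daily for 28 days. The visit dates themselves are clear.

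**What to change.** In *Outcomes for feasibility and efficacy*, name one primary efficacy estimate. A natural choice is the between-group difference in change in ESS from baseline to day 28. ESS is the entry scale and measures the target symptom, and day 28 ends the treatment course. Day 90 is also a planned visit and could be defended. What matters is that one visit is fixed before unblinding.

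Label the other 15 comparisons secondary or exploratory. Report each as an estimate with a 95% confidence interval and no significance claim, and say which estimate will be used to size phase 2. Call days 7 and 14 on-treatment assessments. If the trial registration carries the same open definition, align it.

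A Bonferroni correction over all 16 would also control the error rate, but at 20 per group it costs much power (81% falls to 46% in the illustration above), so a single named estimate suits this pilot better.

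The cost is wording only, with no new data or visits. The sponsor gives up significance claims on the other 15 comparisons.

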### Randomization

All registered patients will be randomly assigned to the intervention group or the control group with a ratio of 1:1. Randomizing the sequence column order will be performed according to the predefined table generated by a computer software program. The random sequence will be hidden in a closed opaque envelope. Before initiating the study, the envelopes will be prepared by research assistants who are not directly involved in the research project. After recording baseline measures, participants will be randomly allocated to either the RIC or control group by the treating physicians who will open the sealed opaque envelopes.

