**Figure 2 F2:**
[figure not shown]
Procedure timeline **(A)** RIC group; **(B)** Control group (Sham-RIC).

Epworth Sleepiness Scale, the Pittsburgh Sleep Quality Index (PSQI), and Parkinson's Disease Sleep Scale-2 (PDSS-2) are to be used to assess the common sleep problems of Parkinson's patients (44, 45). The Parkinson's Disease Questionnaire 39 (PDQ39) is to be used to assess the quality of life of Parkinson's patients (46), which is administered by trained investigators blinded to the treatment assignment. The assessments are performed on the day of enrollment for baselines and 7, 14, 28, and 90 days after the enrollment.

Patients will continue their home medications to manage chronic conditions, including Parkinson's disease, according to the recommendations of the International Parkinson and Movement Disorder Society (15, 47).

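### Primary feasibility item (1), whether the scales can be performed, is uninformative for ESS at baseline and biased towards 100% at follow-up by the completers-only rule

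*Protocol article*

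**What the plan says.** The section on outcomes for feasibility and efficacy names two things the study will determine as part of its primary outcome. Item (1) is "whether ESS, PSQI, PDSS-2, and PDQ39 can be performed in the patients". Item (2) is the difference in scores between patients with and without RIC. The primary outcome is change "from the baselines to post-treatment on days 7, 14, 28, or 90".

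Four other statements bear on item (1):

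- **Entry.** Under Patient population, the enrollment criteria include "3) ESS score ≥10", and the section repeats: "In this study, those with ESS ≥ 10 are recruited". PSQI, PDSS-2 and PDQ39 are not among the criteria.
- **Sequence.** Under Randomization: "After recording baseline measures, participants will be randomly allocated to either the RIC or control group".
- **Schedule.** Under Interventions, after the Figure 2 caption: "The assessments are performed on the day of enrollment for baselines and 7, 14, 28, and 90 days after the enrollment".
- **Analysis set.** Under Statistical analysis: "Data are obtained from all patients who complete the study protocols and follow-ups". The next sentence there says the analysis is per protocol. No other analysis set is named.

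**The concern.** A completion outcome is useful only if patients who fail it stay in the denominator. Here one rule removes possible failures before entry (for ESS) and another removes them after randomisation (for all four scales). A high completion figure could then reflect who was counted and say little about how patients coped with the questionnaires.

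The question is a real one in this population. Patients may be up to 90 years old, consent may come from a legal representative, and the Discussion says that different disease stages will be included. The sample size section says the results will be used to judge feasibility and to plan the phase 2 sample size. An inflated completion figure would support the first use wrongly. It would also hide missing forms that a later trial would have to allow for.

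**Working it through.** The article states no completion rate, target or threshold for item (1), so there is no figure of its own to reproduce. The check takes baseline and follow-up in turn.

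**Inputs from the article.** 40 patients, 20 per group (Study design); four scales; one baseline and four follow-up assessments (Interventions); ESS of at least 10 for entry (Patient population); data from completers only, per protocol (Statistical analysis).

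**Assumed input.** d, the number of randomised patients who do not complete the scales at a given follow-up visit and are left out of the completer set for that reason. The article gives no value, so a range is shown.

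**Step 1, baseline.** A patient cannot meet the ESS criterion without an ESS score. Baseline ESS completion among enrolled patients is therefore 40/40 whatever the true difficulty of the scale. For the other three scales the article gives only an order of events, with measures recorded before allocation. Completion may well be near full, but no rule fixes it.

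**Step 2, follow-up, all randomised.** Each scale is due 40 × 4 = 160 times after randomisation, or 160 × 4 = 640 forms over the four scales. Neither the entry rule nor the order of baseline and allocation determines any of these. At a given visit, completion among randomised patients is (40 − d)/40.

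**Step 3, follow-up, completer set.** If finishing follow-up includes finishing the scales, the d patients leave both numerator and denominator, and completion is (40 − d)/(40 − d) = 100% for every d. The overstatement is d/40.

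**Step 4, numbers.** The exact (Clopper-Pearson) 95% limits for x of n are the 0.025 quantile of Beta(x, n − x + 1) and the 0.975 quantile of Beta(x + 1, n − x). For x = n the upper limit is 1 and the lower limit is 0.025^(1/n), so 40/40 gives 0.025^(1/40) = 0.912.

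| Assumed d | Completer set | All randomised | Exact 95% CI, all randomised | Overstatement |
|---|---|---|---|---|
| 0 | 40/40 = 100% | 40/40 = 100% | 91.2% to 100% | 0 points |
| 2 | 38/38 = 100% | 38/40 = 95% | 83.1% to 99.4% | 5 points |
| 4 | 36/36 = 100% | 36/40 = 90% | 76.3% to 97.2% | 10 points |
| 8 | 32/32 = 100% | 32/40 = 80% | 64.4% to 90.9% | 20 points |

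The completer column does not change with d, so under this rule it cannot tell 0 failures from 8. A patient who completes early visits and stops later affects the comparison only from the visit at which the form is missing. For earlier visits that patient's completed forms are simply lost from the count.

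**The case against.** **The stronger reading.** A reader might infer that scale completion is 100% by construction throughout, since ESS is required for entry and baseline is recorded before allocation. The article does not support that. Those two facts make the result certain only for baseline ESS. The enrollment criteria name none of the other three scales, and nothing says that an incomplete form bars randomisation. Nor do these facts settle follow-up. If each patient completed a scale at a visit independently with probability 90%, 95% or 99% (assumed), the chance that all 40 do so is 0.90^40 = 1.5%, 0.95^40 = 12.9% or 0.99^40 = 66.9%. Full completion among randomised patients is not guaranteed.

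**The completer rule may not mean every form.** A patient could attend every visit and still leave one scale unscorable, and so remain in the set as a failure. This stands, and it is why the completer figure is given as up to 100%. The direction of the bias is unchanged, because anyone removed for not completing is a failure removed.

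**The per-protocol rule may not govern a descriptive count.** This is possible. However, the article states one rule for where its data come from and makes no exception for item (1), so following the text as written gives the biased count.

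**Completion definitions are usually left to the full protocol or SAP.** That is true, and their absence is not the point here. The point is that a stated analysis rule works against a stated primary outcome.

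**A denominator of approached or screened patients.** It may seem natural to ask for this as well. It answers a different question: item (1) refers to the trial's patients, and people who decline or score below 10 on ESS have no stated reason to be given the other three scales. Setting a rate in approached patients against one in enrolled patients would mix two populations.

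**Conclusion.** The concern holds in a limited form. For ESS at baseline, item (1) is uninformative because the entry rule fixes the answer. At days 7, 14, 28 and 90 it is biased towards 100%, because patients who could not complete the scales leave the denominator. The bias is d/40: 10 percentage points with an assumed 4 non-completers, and 5 to 20 points over an assumed range of 2 to 8. With no non-completers there is no bias.

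This rests on two readings: that the completers-only rule applies to item (1), and that finishing follow-up broadly includes finishing the scales. Both are natural readings of the text, but neither is spelled out. The documents do not show that no patient can fail at any visit. They also set no threshold that an inflated rate would falsely meet.

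**What to change.** In the outcomes section, define item (1) as the proportion of randomised patients with each scale fully completed at days 7, 14, 28 and 90, by scale and by visit, with a form not obtained counted as not completed. In the Statistical analysis section, state that item (1) is exempt from the completers-only, per-protocol rule. Do not present baseline ESS completion as evidence of feasibility.

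The denominator at each visit is then 40, or 20 within a group, which the trial already knows. No screening-log denominator and no extra patients, visits or questionnaires are needed. The cost is two wording changes and keeping count of missing forms for patients who stop. The downside is that the reported completion rate may be lower.
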